### Main outcome measures

WP1—all-cause 30-day mortality (the proportion of patients who die from any cause within 30 days of the date of their event) calculated from linked MINAP and Office for National Statistics (ONS, Civil Registry) mortality data.

Proportion of eligible patients for whom PHECG performed over time.

WP2—factors that may influence the use of PHECG in ACS (eg, patient symptoms, prehospital diagnosis, recognition of ACS, EMS clinician training level and gender, patient refusal, patient ethnicity, language spoken, capacity to communicate and/or consent).

WP3—an understanding of influences on clinical decision-making regarding recording of the PHECG in ACS (and thereby, potential explanations of quantitatively measured rates of PHECG use).

### Estimated sample size

WP1: all eligible patients in MINAP will be included in analysis. Formal power calculations are therefore unnecessary, but we anticipate that data extraction and linkage will generate a dataset comprising over 500 000 cases.

WP2: we will sample 1650 cases at random from the MINAP database using a stratified sampling method. We will oversample by 10% (165 cases) to allow for any cases where the corresponding EMS clinical records cannot be located. Based on information received from NICOR, we expect approximately a 2:1 ratio of PHECG cases to non-PHECG cases (NICOR, personal communication). Assuming this, we will have 80% power (using 5% significance) in detecting a standardised statistical effect of 0.15.

WP3: six EMS clinician focus groups (two per EMS), each comprising up to eight participants, will be convened, purposively sampling to capture the views of staff in both urban and rural settings within large EMS. We aim to obtain depth with a sample size that is neither too small to contain various aspects of the phenomenon nor too large to allow depth of analysis in this qualitative study.^23^

### Data collection

WP1: we will use existing MINAP registry data, collected prospectively at each hospital using a secure electronic system, encrypted and transferred online to a central database in which patient identity is protected.^21^ We will link MINAP data to ONS Civil Registry mortality data at individual level through NHS Digital.

WP2: we will randomly select a cohort of patients with and without PHECG, with ACS recorded in MINAP, for the three participating EMS using a unique identifier for patients in MINAP who came to hospital via EMS. The sample will be stratified by preagreed demographic variables (such as sex and age band) to ensure it is sufficiently representative. We will report key characteristics of the sample, those of the MINAP ACS subpopulation (those who came via EMS), and the overall MINAP population.

We will employ and train paramedic researchers at each site to retrieve and extract data from the EMS records of each sampled patient. We will collect data on factors that may influence the use of a PHECG which are not recorded in MINAP, including coded data on patient symptoms, prehospital diagnosis of ACS, EMS clinician training level and sex, patient refusal, patient ethnicity, language spoken, capacity to communicate and/or consent. The paramedic researchers will extract relevant narrative data from the ‘free-text’ section within EMS records. A second researcher will independently extract data for a random sample of 10% of the cases for quality assurance purposes.

WP3—we will conduct focus groups using a semistructured approach, aiming to explore the views of EMS clinicians about the role of PHECG, experiences of assessing patients with STEMI and non-STEMI, and influences on whether or not to record a PHECG. A topic guide will be constructed in the context of the quantitative findings and with input from EMS clinicians, patient and public representatives, and in the context of literature that highlights complexity and multiple influences on decisions made in the EMS setting. Focus group discussions will be digitally recorded and transcribed verbatim. Participants will be briefed at recruitment and at the beginning of each focus group not to disclose any information that might serve to identify individual(s).

### Analysis

WP1—available demographic data will be presented using interval categories for continuous variables where appropriate. We will present mortality as (1) the proportion occurring within 30 days of hospitalisation, and (2) time to death, summarised using Kaplan-Meier survival curves. We will estimate (with 95% CIs) the outcomes associated with the performance of PHECG via a binary variable, adjusting for other statistically significant demographic and clinical variables.

A similar modelling approach will be used for other categorical variables of interest (for instance, use of reperfusion); natural extensions within the framework of generalised linear models will cover both the analysis of any counts and measurement outcomes of interest.

WP2—partitioning our sample of ACS cases by PHECG or not, we will use univariate and multivariate analyses to explore differences in patient symptoms and other factors between these two groups; we will report and explore differences across stratifying variables (such as age band, sex), and across categorisations emerging from consideration of free-text narratives in EMS records). We will use binary logistic regression to explore the extent to which factors are associated with PHECG use or not in ACS cases, reporting odds ratios (with 95% CIs) for statistically significant variables. Inter-rater reliability of data retrieval will be assessed using Cohen’s kappa.

WP3—focus group transcripts will be managed using NVivo software.^24^ Initially, we will conduct an inductive thematic analysis, using bracketing, and with iteration to the coding framework based on deep reading of the data, discussion within the research team and member checking. We will then use framework analysis^23^ and analyse whether the generated themes show consensus or dissent when considered against any differences in the characteristics of the focus group participants (eg, grade of EMS clinician, local practice). At least two researchers will read, reread and draft a coding framework for discussion and blinded application to at least two transcripts. The coding framework will be developed iteratively by discussion throughout the analysis process. Researchers involved in the qualitative data collection and analysis will meet regularly to reflect on their assumptions, personal influences and data interpretations.

WP4—evidence from the WPs will be presented to a wider consultative group of study participants including local EMS collaborators and patient and public representatives. This wider group will be invited to discuss and help the research team interpret the emerging findings. WP leaders will collaborate through discussion to reach agreement on the evidence against each research question.

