Since our earlier study there has been significant change in reperfusion strategies for STEMI in the UK, with primary percutaneous coronary intervention (pPCI) superseding fibrinolytic treatment as the treatment of choice.^18^ This has required changes in EMS organisation and practice, including direct transportation to pPCI-capable hospitals and the atrophy of existing programmes of prehospital administration of thrombolytic treatment by ambulance paramedics.

Considering this major change in practice and an increased emphasis on PHECG in guidelines, we expected there to be an increase in the use of PHECG since our first report. On the contrary, it appears to have declined to 64% for STEMI and 44% for non-STEMI, respectively, in 2015–2016 (National Institute for Cardiovascular Outcomes Research (NICOR), personal communication). It is therefore timely to update our analysis on a more recent cohort of patients and to explore potential determinants of why PHECG is/is not recorded.

Our a priori hypotheses are:

PHECG use by EMS personnel is associated with more timely processes of care and a lower short-term mortality rate in patients with suspected ACS, for both STEMI and non-STEMI cases.Patients who do not receive a PHECG systematically differ from those who do.EMS clinician decision-making regarding PHECG is influenced by more than clinical (pathophysiological) characteristics.It is possible to use the findings from this study as the first stage of the development and subsequent evaluation of a complex intervention^19^ designed to improve the uptake of PHECG.

Our research questions (with their respective work packages (WP)) are:

For patients presenting to EMS with suspected ACS, is there a difference in 30-day mortality and reperfusion strategy in patients managed outside hospital by EMS between those who do and those who do not receive a PHECG? (WP1)Has the proportion of eligible patients who received a PHECG changed since the national rollout of pPCI networks? (WP1)Are patients that receive a PHECG different from those that do not in terms of social and demographic factors, and in their prehospital clinical presentation? (WP2)What factors do EMS clinicians report as influencing their decision to perform a PHECG? (WP3)

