### Study population

WP1: patients will be eligible for the study if aged 18 years or older when attended by EMS and admitted with ACS between 1 January 2010 and 31 December 2017 to one of 228 participating hospitals in England, Wales and Northern Ireland mandated to enter data into MINAP. For patients with multiple admissions, only the earliest record of their ACS event in MINAP will be used.

MINAP is overseen by a multiprofessional Domain Expert Group of stakeholders within the National Cardiac Audit Programme (NCAP). As such, this study will include data collected on behalf of the British Cardiovascular Society under the auspices of NCAP, in which patient identity is protected.^21^

WP2 will include a stratified random sample of patients with suspected ACS (by initial diagnosis in MINAP) attended by one of the three participating EMS during the study period. It will include those with or without PHECG.

WP3 will include a purposive sample of EMS clinicians of different clinical grades, with varying levels of experience in caring for patients with ACS in the prehospital setting, who are trained in the use of PHECGs and employed by one of the three participating EMS.

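### The stated WP1 adjustment rule does not provide for admission year, so the PHECG–outcome estimates over 2010–2017 are open to confounding by calendar time

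*Protocol article*

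**What the plan says.** The Analysis section of the protocol article says that the outcomes associated with PHECG will be estimated with PHECG as a single two-level term, "adjusting for other statistically significant demographic and clinical variables". It plans a similar approach for other categorical outcomes and gives use of reperfusion as the example. It names neither admission year nor calendar period as a covariate, and it describes no PHECG estimate by period.

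The Study population section takes patients "admitted with ACS between 1 January 2010 and 31 December 2017", which is eight calendar years.

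Elsewhere, time is a subject of study. The second research question in the Introduction asks: "Has the proportion of eligible patients who received a PHECG changed since the national rollout of pPCI networks"? The Main outcome measures section lists the proportion of eligible patients with a PHECG over time as a WP1 outcome. The Introduction also says of PHECG use that "it appears to have declined to 64% for STEMI and 44% for non-STEMI" in 2015–2016, and it describes a change in reperfusion strategy, "with primary percutaneous coronary intervention (pPCI) superseding fibrinolytic treatment as the treatment of choice".

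**The concern.** Calendar year confounds the PHECG–mortality comparison if, within the window, both the share of patients with a PHECG and the risk of death change with year. Patients with a PHECG then come disproportionately from years of higher or lower mortality, and a pooled contrast credits or charges that difference to the PHECG. The same holds for reperfusion, whose background use the protocol describes as changing.

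The protocol takes the first condition seriously enough to make it a research question. The adjustment rule for the first research question, on the same patients, makes no matching provision. Admission year is neither a demographic nor a clinical variable, so an analyst who follows the rule literally would leave it out. If year were admitted as a candidate, its retention would rest on a significance test, which is not a test of confounding.

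The effect to be re-estimated is small. The Introduction gives the earlier odds ratio as 0.94 (95% CI 0.91 to 0.96), so a bias of a few per cent would matter to the conclusion.

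**Working it through.** WP1 has no power or precision figure to reproduce. The question is how far leaving out year could move the odds ratio.

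**Inputs from the protocol article**
- Eight admission years (Study population).
- About a third of patients without a PHECG in the earlier work, so about 67% with one (Abstract).
- PHECG use of 64% in STEMI and 44% in non-STEMI in 2015–2016 (Introduction).
- Earlier 30-day mortality of 7.4% vs 8.2%, and odds ratio 0.94 (Introduction).
- Over 500 000 cases expected (Estimated sample size).

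**Assumptions, none of them in the documents**
- Years of equal size and linear trends.
- A STEMI share of 40%, which gives overall PHECG use of 0.40 × 64% + 0.60 × 44% = 52%.
- 67% and 52% as the two ends of the window.
- All mortality levels by year.
- No PHECG effect within any year, so any departure of the pooled odds ratio from 1 is bias.

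**Formula.** With PHECG share p and mortality m in each year, identical in both groups, pooled mortality is Σpm / Σp with a PHECG and Σ(1−p)m / Σ(1−p) without.

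**Worked case: PHECG use 67% to 52%, mortality 9% to 7%**
- Mean p = 0.595 and mean m = 0.08, so Σp = 4.76, Σ(1−p) = 3.24 and Σm = 0.64.
- Σpm = 0.3834, so Σ(1−p)m = 0.2566.
- With a PHECG: 0.3834 / 4.76 = 8.05%. Without: 0.2566 / 3.24 = 7.92%.
- Odds ratio = (0.0805 / 0.9195) / (0.0792 / 0.9208) = 1.018 (from unrounded values).

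**Range, with a true odds ratio of 1 in every row**

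| PHECG use | Mortality | Pooled OR | Shift in log OR as share of \|log 0.94\| (0.0619) |
|---|---|---|---|
| flat | any | 1.000 | 0% |
| any | flat | 1.000 | 0% |
| 67% to 52% | 9% to 8% | 1.009 | 14% |
| 67% to 52% | 9% to 7% | 1.018 | 29% |
| 67% to 52% | 10% to 7% | 1.026 | 42% |
| 72% to 50% | 10% to 7% | 1.039 | 62% |
| 52% to 67% | 9% to 7% | 0.982 | −29% |
| 50% to 72% | 10% to 7% | 0.963 | −62% |

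Falling use with falling mortality biases towards harm. Rising use with falling mortality produces a spurious benefit.

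**Check with a different shape.** Take two equal halves with a step between them and a true odds ratio of 0.94. PHECG use 60% then 50% with mortality 9% then 7% gives a pooled 0.967. Use of 50% then 60% with the same mortality gives 0.915. A 20-point drop in use, 70% then 50%, gives 0.998. With mortality flat, the pooled value stays at 0.940 to 0.942. Adjusting for period returns 0.94 in each case. An abrupt change can therefore do more than the linear trends tabulated above.

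**Against precision.** Using 7.4% and 8.2% at 500 000 cases, the standard error of the log odds ratio is about 0.011. The linear shifts of 0.009 to 0.038 on the log scale are then about 0.8 to 3.5 standard errors. More cases narrow the interval around the shifted value and do not move it back.

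No comparable calculation is possible for reperfusion, because the documents give no reperfusion rates.

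**The case against.** **The article is condensed.** It gives one sentence on adjustment and no covariate list, so it does not name age or sex in that sentence either. A fuller list, with year in it, may sit in a document not shown. A reader might infer that the model adjusts for demographic and clinical variables only; the text does not say that. This stands, and silence about year would not by itself be a finding. What remains is that the article states a rule, by type of variable and by significance, and that rule does not provide for a variable which the protocol's own second question makes relevant.

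**Confounding is not shown.** A reader might infer that the estimate is confounded, or that patients with a PHECG are concentrated in the earlier years. The documents support neither. The decline to 64% and 44% is set against the earlier report, not against 2010. The second question asks whether use changed and does not assume that it did. The Estimated sample size section expects about 2:1 PHECG to non-PHECG in the WP2 sample, which is about 67% and not 52%, though that concerns three services. Mortality by year appears nowhere. This stands in full, and it is why the range includes zero and both signs.

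**Two treatment eras.** A reader might also infer that the window mixes a fibrinolysis era with a pPCI era. The reperfusion change is dated only by "Since our earlier study there has been significant change in reperfusion strategies for STEMI in the UK"; the rollout is undated, and so is "the atrophy of existing programmes of prehospital administration of thrombolytic treatment by ambulance paramedics". The article presents the data as a more recent cohort in the pPCI era. The stronger reading is not supported.

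**The comparison with 0.94 is rough.** The earlier 7.4% vs 8.2% gives a crude odds ratio of (0.074/0.926)/(0.082/0.918) = 0.895, so 0.94 appears to be adjusted, while the shifts above come from an unadjusted collapse. Clinical covariates could absorb part of a mortality trend. This also stands: the percentages show scale and do not predict the bias.

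**The p-value clause may hardly matter.** At 500 000 cases, even a linear fall in mortality from 9% to 8% gives a z of about 8, so significance screening would keep year if it were a candidate. That is fair, but the stated rule does not make it one.

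The protocol's acknowledgement that an observational design prevents causal inference does not answer the point. Admission year is measured and at hand, and a variable of that kind can be adjusted for.

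**Conclusion.** The point holds as an exposure to bias, not as a demonstrated bias. The stated WP1 rule does not provide for admission year across an eight-year cohort, although the protocol treats PHECG use as possibly changing over time. The PHECG estimates are therefore open to calendar-time confounding if mortality or reperfusion practice also moved within 2010–2017.

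Size and direction cannot be determined from the documents. Under the assumed linear trends the mortality odds ratio shifts by roughly 0 to 4% in either direction. It does not shift if either trend is flat, and it could shift more if the changes were abrupt. The upper part of that range is appreciable against an earlier estimate only 6% below 1. The change is worth making because it is nearly free, and the conclusion does not depend on any one scenario being true.

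**What to change.** State that admission year, as a categorical variable, enters every WP1 model relating PHECG to 30-day mortality or reperfusion, whatever its p-value. As a secondary check, report the PHECG estimate by period, for example from a PHECG-by-period term with the periods fixed in advance, beside the pooled estimate. This also shows whether the pooled figure describes the most recent years.

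The cost is a line of analysis wording. Admission date is already needed for eligibility and for the second research question, so no new data are required. Seven extra parameters (eight years less one reference year) cost negligible precision at about 500 000 cases.

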## Methods and analysis

To answer our research questions an explanatory, mixed-method study will be undertaken,^20^ in which the qualitative data will be used to aid understanding of the quantitative findings, consisting of the following four WPs:

*WP1—population-based, linked cohort study using Myocardial Ischaemia National Audit Project (MINAP) data from 2010 to 2017* to update evidence on care and outcomes for patients eligible for PHECG. MINAP is a comprehensive registry of ACS hospitalisations mandated by the Department of Health. Each MINAP entry provides patient demographic and clinical details of the patient journey across 122 data items. Data collection and management have been described previously.^21^

*WP2—retrospective chart review*^22^*of EMS records* to collect data on factors recorded by EMS staff that may be associated with PHECG use, but are not routinely collected in MINAP.

WP3—EMS clinician self-report on PHECG recording, using focus groups.

*WP4—synthesis of the findings from WP1, WP2 and WP3*. This will be conducted to address our research questions, within our aim of using qualitative findings as explanatory of quantitative results^20^ and with the understanding that these data are intended as the development phase for the design of a complex intervention for further testing.^19^

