### Strengths and limitations of the study

The main limitation of the study is its observational, cross-sectional nature, which prevents us from inferring causal relationships. Retrospective chart review methods, although commonly used in emergency research, are not without shortcomings^22^; for example, they are subject to bias by the data abstractors’ through misinterpretation of chart entries or miscoding of data during data abstraction leading to either random or systematic errors. To minimise the effect of those shortcomings, recommended measures from published methodological standards^22^ have been implemented in the design of WP2.

The main strengths of the study are the very large population included in WP1, and its multifaceted, multicentre approach to understanding barriers and facilitators in performing PHECG.

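### WP2 compares PHECG and non-PHECG cases on free-text note categories whose recording can depend on whether the ECG was done, so a factor can appear associated through note-writing alone

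*Protocol article*

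**What the plan says.** Under Methods and analysis, the purpose of the WP2 chart review is "to collect data on factors recorded by EMS staff that may be associated with PHECG use". The predictors are therefore what attending staff wrote in routine records.

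Under Data collection, a list of coded items includes patient refusal, language spoken and capacity to communicate or consent. A separate sentence covers the free-text section: "The paramedic researchers will extract relevant narrative data". A second researcher re-extracts a random 10% of cases.

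Under Analysis, cases are partitioned by PHECG or not. Differences are explored across stratifying variables and "across categorisations emerging from consideration of free-text narratives in EMS records". A separate sentence plans binary logistic regression of PHECG use on factors, with odds ratios and 95% CIs reported for the statistically significant ones. Agreement between extractors is assessed with Cohen's kappa.

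Under Strengths and limitations, the example given of a chart-review shortcoming is "misinterpretation of chart entries or miscoding of data during data abstraction". The article adds that measures from published standards have been implemented, and that the observational design rules out causal inference.

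**The concern.** The clinician who did or omitted the ECG also wrote the note. A narrative tends to explain what needs explaining. A difficulty with the patient may be written down when there is no ECG to show, and left out when the ECG was obtained despite it. Recording of the predictor can then depend on the outcome.

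Refusal is the plainest case. If the item means refusal of the ECG, it is close to a restatement that no ECG was done, yet it is listed among the factors that may influence PHECG use.

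The stated safeguards act at another step. Duplicate extraction and kappa test whether two readers take the same content from the same note. Two readers can agree perfectly on a selectively written note.

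At stake is the third hypothesis, which looks for influences beyond clinical characteristics. The quantitative findings also feed the WP3 topic guide and the WP4 synthesis, from which an intervention is to be developed. Reporting odds ratios only for significant factors makes an artefact of this kind more likely to be among those shown.

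**Working it through.** **Inputs from the article (Estimated sample size).** "we will sample 1650 cases at random from the MINAP database using a stratified sampling method"; "we expect approximately a 2:1 ratio of PHECG cases to non-PHECG cases". This gives 1650/3 = 550 non-PHECG and 1100 PHECG cases. The 165 extra cases cover records that cannot be found, so 1650 is taken as the analysed number.

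**The plan's own figure.** The article says "we will have 80% power (using 5% significance) in detecting a standardised statistical effect of 0.15". Two-sided: 0.15/√(1/550 + 1/1100) = 2.87, and Φ(2.87 − 1.96) = 81.9%. The stated 80% reproduces. It does not bear on this point, but it confirms the group sizes used below.

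**Assumed inputs, not in the article.** True prevalence of a factor is p in both groups, so the true odds ratio is 1. If present, the factor is written down with probability s₀ in non-PHECG notes and s₁ in PHECG notes. A factor not mentioned is counted as absent.

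**Formulas.**
- Recorded prevalence: b = p·s₀ (non-PHECG) and a = p·s₁ (PHECG).
- Recorded odds ratio, non-PHECG v PHECG: [b/(1 − b)] / [a/(1 − a)].
- Unpooled standard error: SE = √(b(1 − b)/550 + a(1 − a)/1100), and z = (b − a)/SE.
- Chance of a significant result in the false direction: Φ(z − 1.96). A test with pooled variance under the null gives the second percentage below.

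**One case in full: p = 5%, 80% v 40%.** b = 0.05 × 0.80 = 0.040 and a = 0.05 × 0.40 = 0.020. The odds ratio is (0.040/0.960)/(0.020/0.980) = 2.04. SE = √(0.04 × 0.96/550 + 0.02 × 0.98/1100) = 0.00936, so z = 0.020/0.00936 = 2.14 and Φ(0.18) = 57%. The pooled test gives 65%.

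| Prevalence | Recorded, non-PHECG v PHECG | Recorded rates | Odds ratio | Significant (unpooled; pooled) |
|---|---|---|---|---|
| 10% | 90% v 80% | 9.0% v 8.0% | 1.14 | 10%; 11% |
| 5% | 80% v 60% | 4.0% v 3.0% | 1.35 | 17%; 20% |
| 10% | 75% v 50% | 7.5% v 5.0% | 1.54 | 48%; 53% |
| 5% | 80% v 40% | 4.0% v 2.0% | 2.04 | 57%; 65% |
| 10% | 80% v 40% | 8.0% v 4.0% | 2.09 | 87%; 91% |

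Equal recording (50% v 50%) gives an odds ratio of 1.00 and the nominal 5%. With PHECG use as the regression outcome the odds ratios are the reciprocals, for example 1/2.04 = 0.49. The figures are for one unadjusted factor and ignore the stratified sampling.

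**The case against.** Several counterpoints stand and limit what can be claimed.

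- **Causes.** A reader might infer that the plan models note-derived factors as causes. It does not: the Analysis section speaks of association, and the limitations disclaim causal inference. That disclaimer does not answer the present point, because here the association itself may be an artefact.
- **Language and capacity.** These look like natural examples of biased free text, but Data collection lists them as coded data. Whether the codes come from fixed fields or from the narrative cannot be settled without the extraction form. Clinician sex and training level should be little affected.
- **Free text as regressors.** The sentence on free-text categories plans a comparison, and the regression sentence says only factors. That emergent categories enter the model is an inference.
- **Mechanism and direction.** The article neither states nor measures that difficulties are noted more often when the ECG is missing. Its remark about defensive motives concerns clinical decisions. The reverse is possible: a fuller work-up may bring a fuller note and mask a barrier.
- **Limitations wording.** Abstractor error is introduced as an example, and the published standards are not visible, so what they cover cannot be judged.
- **Context.** WP2 is exploratory, WP3 gathers clinicians' own accounts, and any intervention would be tested later in a randomised trial. No decision rests on a single odds ratio.

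A condensed article may also leave coding detail to the full protocol. The point does not rest on that gap. It rests on a between-group comparison that the article itself states, and on safeguards that cannot detect this bias.

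**Conclusion.** The point holds as a possibility that the stated comparison leaves open, not as a demonstrated bias. A factor taken from notes can appear associated with PHECG use because of how notes are written, and refusal of the ECG is almost bound to.

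The size is unknown. Across the assumed recording rates the spurious odds ratio runs from 1.14, significant in about 10% of samples, to 2.09, significant in up to about 91%. A mild recording difference does little harm; a two-fold one would usually yield a false finding at 10% prevalence and more often than not at 5%. All of this assumes equal true prevalence, the 550 v 1100 split, and that an unmentioned factor is counted as absent.

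A reader might go further and conclude that WP2's barriers will be inflated, or that free text must be barred from every between-group comparison. The article supports neither: recording rates and direction are not given, and a full bar would give up part of the comparison that the third research question asks for.

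**What to change.** 1. Code each note-derived factor as present, documented absent or not documented.
2. Report the share not documented by PHECG group. A clear difference would be the warning sign that kappa cannot give.
3. Give each odds ratio twice, with not documented treated as absent and as missing. A conclusion that changes between the two depends on documentation.
4. Report stated reasons for not recording an ECG, including refusal of the ECG, descriptively within the non-PHECG group, and not as regressors.
5. Label any between-group comparison of other free-text categories as exploratory and open to differential documentation.
6. Name this limitation beside abstractor error under Strengths and limitations.

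Cost: one extra code per item on the extraction form, some added tables and a few sentences of text. The real loss is that stated reasons for omission will have no odds ratio. The sample size does not change.
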